## 4 Trial Objectives

- To compare the “overall palatability” of the new L-PZQ ODT (without water) and the new racemate PZQ ODT (without water)
- To compare the “overall palatability” of the new L-PZQ ODT (with water), the new Rac-PZQ ODT (with water) and the current racemate PZQ tablets (crushed and dispersed with water) (reference).

Assessment will be done by means of human gustatory sensation tests (100 mm VAS scale modified by the incorporation of a 5 point facial hedonic scale). Primary end point for the taste is the VAS scale taken at 0 min. The VAS scale obtained at 2 to 5 minutes is a secondary endpoint for the taste. The data will be evaluated using ANOVA with sequence, treatment and stratification factors (age and sex as covariates)

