On Day 2, the subjects will assess the palatability of the following arms in a randomized sequence:

- L-PZQ ODT (150 mg) dispersed in water administered in the mouth cavity
- Rac- ODT (150 mg) dispersed in water administered in the mouth cavity
- 150 mg current PZQ tablet (1/4 of a 600 mg tablet) crushed, dispersed in water and administered in the mouth cavity

Gustatory sensation studies will be performed on the different formulations immediately after tasting and 2-5 min after the study drug has been spat out.

All volunteers will be asked to place a mark along the line with the use of a 100 mm visual analogue scale (VAS) that incorporates a 5 points hedonic scale for “overall palatability”.

In addition, any discomfort or other observation in relation to acceptance of the study medication (e. g. spitting out of the medicine) will be reported by the parents or investigator.

An open ended questionnaire (description of mouth feeling and taste description) will be conducted for each child during the washout period.

After the trial a therapeutic dose of Praziquantel will be made available to the local health council and management team to provide to the participating school.

**Planned number of subjects:** 48 healthy children (1:1 female/male ratio) will be randomized Children age 6-8 and 9-11 will be stratified in 2 equal groups to have a representative number of children across the full age range 6-11 years.

**Primary endpoints:** Primary endpoints are results from Visual Analogue score (VAS score) assessments (100 mm VAS scale modified by the incorporation of a 5 point facial hedonic scale). Primary endpoint point for the taste is VAS taken at 0 min.

The data will be evaluated using ANOVA with time, sequence, treatment and stratification factors (age and sex as covariates)

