#### **8.1 Sample Size**

A total sample size of 48 subjects is considered adequate to fulfil the objective of the study.

Considering the design Day 1 (2 treatments), Day 2 (3 treatments) with the fact that the same subjects will be treated in both days, the stratification constraint by sex (female/male 1:1 ratio) and age (<9 yrs and ≥9yrs 1:1 ratio), the sample size should be a multiple of 24.

DAY 1: A total of 48 subjects (24 subjects per sequence) will provide at least 89.2% power to detect a 10 pts mean difference in VAS overall palatability between Rac-PZQ ODT (no water) and L-PZQ ODT (no water), assuming a within-subject standard deviation of 15 pts (square root of within subject MSE), and a two-sided type 1 error of 5.0%.

DAY 2: A total of 48 subjects (8 subjects per sequence, 6 sequences due to 3 treatments-3 periods) will provided at least 92.4% power to detect a 20 pts mean difference in VAS overall palatability between one of the new formulations Rac-PZQ (with water) or L-PZQ (with water) and the current PZQ formulation crushed in water, assuming a within-subject standard deviation

of 15 pts (square root of within subject MSE), and a two-sided type 1 error of 2.5%, to adjust for the multiplicity.

Software East 6.2 was used for the sample size calculation.

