### **8.5.2 Analysis of Primary Endpoints**

VAS at time t0 will be summarized using descriptive statistics (mean, median, standard deviation, quartiles (25th, 75th), minimum, maximum) by treatment group.

The first alternative hypothesis (HA1) that the two formulations Rac-PZQ (no water) and L-PZQ (no water) differ in taste, as opposed to the H01 (the two formulations are similar) will be tested using a repeated measure ANOVA with factors time, sequence, treatment and stratification factor of sex and age (in categories). A contrast statement at Time 0 to compare the two formulation based on the likelihood ratio test will be conducted at two-sided 5% significance level.

The second alternative hypothesis (HA2) that at least one of the two new formulations (with water) differs in taste from the “current PZQ formulation” will be tested using a repeated measure ANOVA with factors time, sequence and treatment and stratification factor of sex and age (in categories) will be used.

Contrast statement at Time 0 to compare

- Rac-PZQ ODT (with water) vs current PZQ (crushed with water), and
- L-PZQ ODT (with water) vs current PZQ (crushed with water)

It will be done using the likelihood ratio test. These tests will be performed at an alpha level of 2.5% to account for the multiplicity of testing.

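### The primary analysis is stated in three inconsistent forms, and the section 4 form, read literally, does not deliver the stated Day 1 power

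*Protocol*

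**What the plan says.** The protocol describes the primary analysis three times.

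- Section 4 (Trial Objectives): "The data will be evaluated using ANOVA with sequence, treatment and stratification factors (age and sex as covariates".
- Synopsis: "The data will be evaluated using ANOVA with time, sequence, treatment and stratification factors (age and sex as covariates".
- Section 8.5.2 (Analysis of Primary Endpoints), first hypothesis: "tested using a repeated measure ANOVA with factors time, sequence, treatment and stratification factor of sex and age (in categories". It then takes a treatment contrast at Time 0. The second hypothesis uses the same factors.

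None of the three lists names the child, the individual tasting or the period. Only section 8.5.2 says repeated measures. Time is in two of the lists and absent from the third. Age is a covariate in the first two and categorical in section 8.5.2.

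The sample size rests on a within-child comparison. Section 8.1 says for Day 1: "A total of 48 subjects (24 subjects per sequence) will provide at least 89.2% power to detect a 10 pts mean difference", "assuming a within-subject standard deviation of 15 pts (square root of within subject MSE), and a two-sided type 1 error of 5.0" per cent. For Day 2 it claims "at least 92.4% power to detect a 20 pts mean difference in VAS overall palatability" with "a two-sided type 1 error of 2.5%, to adjust for the multiplicity". Section 8.3.1 makes the VAS mark at time 0 the primary endpoint, and sections 7.1.2 and 7.1.3 collect a second mark 2–5 minutes after each tasting.

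**The concern.** In a cross-over the formulations are compared within the child, so differences between children in how they use the scale must be removed from the error. An ANOVA with only sequence, treatment, age and sex leaves those differences in. It treats the tastings as if they came from separate groups of children, which contradicts the error term used for sizing.

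Section 8.5.2 points the right way but leaves a second question open. Two marks from one tasting share whatever is specific to that tasting. If both marks enter one model, it matters whether the model recognises the tasting as well as the child.

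The Day 1 comparison of the L-PZQ and Rac-PZQ ODTs is at stake. Section 3 says the more suitable formulation will be selected for further development. Analysts following section 4 and section 8.5.2 would both be following the protocol, yet could reach different Day 1 results.

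**Working it through.** **Inputs from section 8.1.** 48 children; within-child SD 15; Day 1 difference 10 points, two-sided alpha 5%; Day 2 difference 20 points, two-sided alpha 2.5% per comparison. **Assumed, because the protocol gives neither:** the within-child correlation rho, and the share of within-child variance common to the two marks of one tasting.

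**1. The stated Day 1 figure.** SE = 15 × sqrt(2/48) = 3.06. Two marks per child give 96 observations; removing 48 children, one treatment and one period degree of freedom leaves 46. The noncentral t with 10/3.06 = 3.27 and 46 df gives 89.2%, exactly as stated. The figure is that of a within-child test.

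**2. Section 4 taken literally, Day 1, 0-min marks.** Without a child term the model uses the total SD, 15/sqrt(1 − rho). The treatment difference itself still varies with SE 3.06, because each child receives both formulations. Residual df = 96 − 5 = 91, critical value 1.986. The test rejects when the difference exceeds 1.986 × model SE.

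| rho | Total SD | Model SE | Threshold | Power at 10 points | True alpha |
|---|---|---|---|---|---|
| 0.1 | 15.81 | 3.23 | 6.41 | 88% | 3.6% |
| 0.3 | 17.93 | 3.66 | 7.27 | 81% | 1.8% |
| 0.5 | 21.21 | 4.33 | 8.60 | 68% | 0.5% |
| 0.7 | 27.39 | 5.59 | 11.10 | 36% | below 0.1% |

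Example at rho 0.5: power = P(Z > (8.60 − 10)/3.06) = P(Z > −0.46) = 68%. Simulation agrees at 0.3 and 0.5 and gives 37–40% at 0.7.

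**3. Day 2.** With a child term, 20/3.06 = 6.5 standard errors, so power exceeds 99.9%. Without one it is still about 99% at rho 0.7. The stated 92.4% is met in either case.

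**4. Section 8.5.2 with both marks in the model, Day 1.** Let T be the variance shared by the two marks of a tasting and E the remainder, with T + E = 225.

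- *Ordinary repeated-measures reading.* Treatment and time are both within child, and treatment is tested against child-by-treatment. Simulation gives a false-positive rate of 4.6–5.3% and power of 92–98%. The paired analysis of 0-min marks alone gives 4.7–5.3% and 89–90%.
- *Child as the only error level, with treatment-by-time and the contrast at 0 min.* Each child has three within-child degrees of freedom, with expected mean squares E + 2T, E and E. The pooled residual is therefore E + 2T/3, whereas the contrast varies in proportion to T + E. The ratio of true to assumed variance is (T + E)/(E + 2T/3).

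| Shared fraction | Ratio | Rejection rate under the null |
|---|---|---|
| 30% | 1/0.900 = 1.11 | 6.3% |
| 50% | 1/0.833 = 1.20 | 7.4% |
| 80% | 1/0.733 = 1.36 | 9.3% |

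The rate is P(|Z| > 1.96/sqrt(ratio)). Simulation gives about 7% at 50% and 9–10% at 80%.

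**The case against.** The strongest defence is that section 8.5.2 governs. It is the section that defines the primary analysis, it says repeated measures, the trial is called a cross-over throughout, and section 8.1 refers to the within-subject MSE. Section 4 and the synopsis are one-line summaries, and section 8 leaves full details to a SAP that is not at hand. Covariance structure is ordinary SAP content, so its absence is not an error. Much of this stands: in its ordinary sense section 8.5.2 keeps both alpha and power. The defence does not remove the conflict, because the protocol prints different factor lists and two model types, and section 4 does not match its own sizing.

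Three stronger readings are tempting and are not supported.

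- A reader might infer that section 8.5.2 makes time the only repeated factor. It lists time beside sequence and treatment and does not label it so.
- A reader might infer a false-positive rate of about 14% on Day 1. That needs both marks pooled into one treatment effect with the child as the only error level. Section 8.5.2 specifies a contrast at Time 0, for which the rate is about 6–10%, and even that needs a pooled residual the protocol never states.
- A reader might infer that the synopsis model loses the Day 1 power too. With both marks in a plain ANOVA, correlation 0.5 and half the within-child variance shared, simulated power is 94% with a 2.9% error rate. A loss appears at correlation 0.7 (77–80%).

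**Conclusion.** The inconsistency is real and concerns the primary analysis. Section 4, read literally, contradicts the within-subject basis of section 8.1. Day 1 power would then be about 81%, 68% or 36–40% at correlations of 0.3, 0.5 or 0.7, against the stated 89.2%. At correlation 0.1 the loss is negligible (88%). The section 4 test is conservative, so it costs power and does not inflate alpha. Day 2 power is not at risk.

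Section 8.5.2 is sound in its usual sense but incompletely fixed. The 6–10% rejection rate on Day 1 is conditional on a child-only error level with both marks in the model, and on 30–80% of within-child variance being shared within a tasting. The documents do not support saying that power or alpha is lost outright: that depends on which statement the analyst follows and on variance components the protocol does not give.

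**What to change.** Align the synopsis and section 4 with section 8.5.2, and state one primary model in all three places. Fit it separately by day to the 0-min VAS marks, with the child as the random (repeated) unit and with treatment, period, sequence, sex and age group as fixed effects. Test the formulation contrasts against the within-child residual, which is the error term section 8.1 used. Say whether time means the VAS assessment time.

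Analyse the 2–5 min marks in a separate model of the same form. If both marks are kept in one model, add treatment-by-time, so that a contrast at 0 min is defined, and a child-by-formulation (tasting) random effect, so that the two marks of one tasting do not count as independent.

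This changes wording in three protocol places and the matching model line in the SAP. It needs no new data and no more children. The drawback of using 0-min marks alone is that no precision is borrowed from the later marks; the stated 89.2% reproduces from one mark per tasting and does not depend on it.

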### 4.1 Secondary Objectives

- To obtain feedback regarding mouth feeling and taste of the different formulations
- To document any discomfort or other observation in relation to acceptance of the study medication

An open ended questionnaire will be used. Any discomfort or other observation in relation to acceptance of the study medication will be recorded in the CRF.

## 5 Investigational Plan

### 5.1 Overall Trial Design and Plan

The participating primary school has been informally contacted and further formal contacts through the Rufiji district education officer will be established upon ethics approval from MRCC. The children will be recruited from one primary school, in the Rufiji district. Initially pupils will be invited with their parents to school for screening whereas they will be asked to consent/assent in to the study and they will be instructed on how to follow up the taste study procedures. Enrolments will occur in the health facilities in Ikwiriri/Kibiti at the end of successive training.

During a two weeks screening period, children will be tested for their ability to hold 2 ml of any appropriate juice in their mouth for 10 seconds and then expel; and to keep a candy in the mouth for 20 sec. without swallowing it. In addition children will be assessed for gustatory abnormality before inclusion in to the study. This prior assessment will involve the documentation of candidate subjects’ ability to properly differentiate flavours of different drinks. In addition, the children will be trained on how to use a hedonic scale.

Initial screening will happen two weeks ahead of trial test date. All pupils meeting inclusion criteria will be further trained on how to hold a test fluid in their mouth. Those exercises will occur during the up to two weeks preceding the taste study. At the end of the screening activities

subjects who meet the inclusion/exclusion criteria will be asked to return to school for the taste assessments during the weekend. Subjects along with their parents/ legal representative will be asked to report to the study site at least 2 hour prior to the first taste test.

As per study instruction children will be asked to perform a swill and spit test of the taste regimen in the form of L-PZQ ODT and Rac-PZQ ODT (each once put on the tongue or dispersed in water) and the current Praziquantel tablet dispersed in water after crushing.

In order not to stress the children and to ensure the complete washing out period of at least one hour, the 5 taste assessment periods are split over two days. Dispersible tablets will be left to self-disintegration without dissolution in water in the buccal cavity for the two tastings on Day 1 whereas the assessment of the dispersed in water taste candidates will occur on Day 2.

A 1;1 ratio of gender based random assignment will ensure equal distribution of subjects' in groups of equal age categories. Each individual will taste each preparation once making up 5 periods for each sequence of the palatability assessment during the two study days (see Table below)

According to the gender and age each subject will be randomized to one of the sequences.

| DAY 1    |          |          |
|----------|----------|----------|
| PERIOD 1 |          | PERIOD 2 |
| A        |          | B        |
| B        |          | A        |
| DAY 2    |          |          |
| PERIOD 3 | PERIOD 4 | PERIOD 5 |
| C        | D        | E        |
| C        | E        | D        |
| D        | E        | C        |
| D        | C        | E        |
| E        | C        | D        |
| E        | D        | C        |

- A) L-PZQ ODT put and disintegrated in the mouth without water
- B) Rac-PZQ ODT put and disintegrated in the mouth without water.
- C) L-PZQ ODT dispersed in water.
- D) Rac-PZQ ODT dispersed in water
- E) Current PZQ formulation 150 mg crushed in water

For every taste, immediately after spitting and 2-5 min thereafter, the child will be asked to put a mark along the line of the 100 mm visual analogue scale (VAS) incorporating a 5 points hedonic scale. An open ended questionnaire (description of mouth feeling and taste description) will be conducted. A detailed description of the assessment is available in section 7/Appendix III.

After the trial a therapeutic dose of Praziquantel will be made available to the local health council and management team to provide to the participating school.

## 5.2 Discussion of Trial Design

The trial will enrol infected and non-infected children, and diagnosis of schistosomiasis will not be made and is not part of the inclusion criteria. According to the EU guidance “Ethical considerations for clinical trials on medicinal products conducted with the pediatric population” it is acceptable to conduct swill and spit taste study in healthy children. However, following the Advisory Board Expert meeting held in August 2013 in Geneva, inclusion of infected children was deemed appropriate and it was recommended to provide a prophylactic post-medication therapeutic dose treatment of Praziquantel to all children who have participated to the trial after the study ends (according to WHO SOPs). It was also recommended at this Expert meeting to avoid exposing children to unnecessary taste fatigue (due to the unpleasant taste of PZQ and the number of treatment arms), as recommended in the CHMP guidance (CHMP, 2005) and to limit as much as possible the number of tablets of PZQ per treatment arm. Hence, a single tablet (150 mg L-PZQ ODT, 150 mg rac-PZQ ODT or ¼ of the Cesol 600 mg tablet) is administered in the trial. To avoid taste fatigue the 5 taste assessments have been spread over two days.

### 5.2.1 Inclusion of Special Populations

African children will be included in this study.

Children are not small adults and children as the target population is regarded as the most suitable panel for taste assessment of pediatric population.

It is recommended to use children over 6 as children below 4-6 years are not considered to be able to express differences in taste perception.

According to the EU guidance “Ethical considerations for clinical trials on medicinal products conducted with the pediatric population” it is acceptable to conduct swill and spit taste study in healthy children. Therefore, healthy children are also included in the trial (see section 5.2.2., inclusion criteria).

There is only a positive benefit /risk for African children since they will have the possibility to receive a therapeutic dose of PZQ after the study

## 5.3 Selection of Trial Population

Only persons meeting all inclusion criteria and not meeting any of the exclusion criteria may be enrolled into the trial as subjects. Prior to performing any trial assessments not part of the subject's routine medical care, the Investigator will ensure that the subject's legal representative has provided written informed consent following the procedure described in Section 9.2. and that the subject has given assent.

### 5.3.1 Inclusion Criteria

For inclusion in the study, all of the following inclusion criteria must be fulfilled:

1. Children, male or female aged 6-11 years (included). Age will be documented by verifying date of birth available from school admission registries or birth certificates in case they are readily available.
2. Parents or guardians given written informed consent prior to any trial related procedure and child given assent.
3. Able to communicate well with the Investigator, understanding the protocol requirements and restrictions, and willing to comply with the requirements of the entire trial.
4. Subjects should be able to hold 2 ml of any appropriate juice in their mouth for 10 sec., without swallowing it and to keep a candy in the mouth for 20 sec. without swallowing it.
5. Children who are able to properly assess and differentiate flavours of different soft drinks.
6. Children who are able to use a hedonic scale (children will be trained before the study).

### 5.3.2 Exclusion Criteria

Subjects are not eligible for this study if they fulfil one or more of the following exclusion criteria:

7. Unlikely to comply with the protocol requirements, instructions and trial-related restrictions, e.g., uncooperative attitude, inability to return for follow-up visits, and improbability of completing the trial.
8. Children with any condition or dietary habit known to interfere with the sense of smell and taste, ingestion of any medication (except paracetamol)
9. All febrile children or those found with history of any significant illness in the period of two weeks preceding the trial. Significant illness among school children attending classes is defined as presence of high body temperature  $\geq 38^{\circ}\text{C}$ , respiratory and heart rates above normal ranges based on the opinion of the study clinician and presence of severe oral thrush.. Those identified sick children at screening will be referred to clinics for management.
10. Any surgical or medical condition, including findings in the medical history, or any significant disease (including children with history of autonomic dysfunction, bronchospastic disease, known hypersensitivity to any drug or artificial sweetener) that in the opinion of the investigator, constitutes a risk or a contraindication for the participation of the subject in the study or that could interfere with the study objectives, conduct or evaluation.
11. Children who have participated in any clinical investigation within the previous 4 weeks.

### 5.4 Withdrawal from Trial

Subjects can be withdrawn from the study procedures for the following reasons:

- Any serious adverse event (SAE).
- Subject lost to follow-up after several documented attempts to contact them.
- Subject withdrew consent.
- Any events that unacceptably endanger the safety of the subject.
- Subject who inadvertently swallow the medication during more than 1 taste assessment.

If a volunteer fails to appear for Day 2 or cannot complete the 5 taste assessments, efforts (i.e. documented phone calls to parents) will be undertaken to locate or recall the subject or at least to determine his/her health status and the explanation for early termination. Those volunteers that cannot complete 5 taste assessments will be replaced by a volunteer of the same sex and age group.

These efforts will be documented in the volunteer's CRF and source documents.

